### Statistical consideration

#### Sample size

The primary outcome of interest is the proportion of elderly people who report an active role in the decision-making process regarding whether to stay at home or move to a care facility. Our estimate of the sample size is based on our updated reviews of interventions to improve the uptake of SDM [43] and earlier studies in primary care, in which we observed a 20% absolute difference between groups with an expected baseline value of 50% for the active role [44]. Our biostatisticians provided a number of scenarios with ICCs ranging from 0.02 to 0.05 and the number of clusters ranging from 12 to 16. We used a conservative value of ICC of 0.05 as the upper limit. In order to detect a difference of 20% (50% to 70%) between the intervention group and the control group after the intervention with 80% power, and a 5% significance level, we would require a total of 186 clients for an individually randomized trial. In considering an ICC of 0.05 and 16 clusters (CPHSSs), we would need a sample size of 456 clients in total. Allowing for a 10% loss to follow-up, 501 clients will be recruited (32/CPHSS). We will also recruit 5 clients/CPHSS before the intervention. This is deemed a sufficient number to be able to compare CPHSSs (experimental versus control) at trial entry on the basis of their clientele profiles [45].

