### Allocation of participants to trial groups

Potential confounding variables will be controlled by randomization. The unit of randomization will be the CPHSS with stratification by urban or rural setting [27]. For CPHSS enrollment, 2 random lists will be prepared to establish the order in which CPHSSs will be contacted. We will follow this order systematically until the enrollment of 4 urban and 12 rural CPHSSs is complete.

A second randomization will occur after participants have completed their baseline measures. This randomization will be stratified to minimize the differences within groups due to geographic location. Thus, 2 urban and 6 rural CPHSSs will be allocated to each group. Randomization and allocation will be done using computer software, and data will be entered by an experienced, independent biostatistician.

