#### Analysis plan

We will perform a descriptive statistical analysis of organizational (CPHSS/health professionals) and socio-demographic (clients/health professionals) characteristics in order to assure the comparability of the intervention and control groups. Potentially confounding variables, if any, will be introduced as covariates in mathematical modeling analysis. Multilevel modeling will be used to take the hierarchical structure of the data into account by specifying random effects at each of the 2 levels: 1) CPHSS and 2) client. For each outcome analyzed, according to the type of variable (continuous or categorical), the goodness of fit and the assumptions of each model will be assessed. Statistical analysis will be performed using the SAS statistical package [46]. The primary outcome, i.e. the proportion of clients reporting an active role in the decision-making process, will be analyzed through multilevel logistic regression using the GLIMMIX procedure of the SAS program. The least squared mean proportions will be estimated and compared to assess the effect of the intervention on the primary outcome. Secondary outcomes will be comparisons between the 2 groups (intervention, control) using multilevel modeling. The *P* value will be adjusted for any multiple comparison tests. Adjustment for multiple comparisons will only be made for secondary outcomes, using the Bonferroni method. This will avoid significant results being due to chance alone. Analysis will be performed after the pre-intervention data collection (for providing performance feedback during the workshop) and at the end of the trial. We will explore the impact of differences between male and female clients on the primary outcome.

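### The 80% power at ICC 0.05 makes no allowance for only 8 CPHSSs per arm (about 74 to 77% on a between-cluster t reference), and 501 recruits contradicts 32 per CPHSS (512)

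*Protocol article*

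**What the plan says.** All the figures are in the Sample size section of the protocol article. The target is stated as "In order to detect a difference of 20% (50% to 70%) between the intervention group and the control group after the intervention" and continues "with 80% power, and a 5% significance level". For that target, "we would require a total of 186 clients for an individually randomized trial". Clustering is then brought in: "In considering an ICC of 0.05 and 16 clusters (CPHSSs), we would need a sample size of 456 clients in total". On the choice of ICC, after scenarios from 0.02 to 0.05, the section says "We used a conservative value of ICC of 0.05 as the upper limit". The recruitment target follows: "Allowing for a 10% loss to follow-up, 501 clients will be recruited (32/CPHSS").

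Two other sections bear on this. Under Allocation of participants to trial groups, "2 urban and 6 rural CPHSSs will be allocated to each group", so each arm has 8 CPHSSs. Under Analysis plan, the primary outcome "will be analyzed through multilevel logistic regression using the GLIMMIX procedure of the SAS program". The article mentions no small-sample correction in the sample size calculation.

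**The concern.** The arm effect is a contrast between 8 randomized CPHSSs and 8 others. The between-CPHSS variation has to be estimated from those 16 units, which leaves about 14 degrees of freedom, or 13 if the urban/rural stratum is fitted. The usual design-effect calculation inflates the variance for clustering but still takes its critical value from the normal distribution (1.96, against 2.145 on 14 df and 2.160 on 13 df). With this few clusters, that overstates power by several points.

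The stated power is the figure against which a null result will be read. If it is too favourable, a non-significant result will be taken as stronger evidence against a 20-point effect than the design can give.

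The recruitment sentence also carries two different totals, so a reader cannot tell which target governs.

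**Working it through.** **Inputs.** Rates 50% and 70%, 5% significance, 80% power, ICC 0.05, 16 CPHSSs, 456 clients analysed, 10% loss, 501 recruits and 32 per CPHSS all come from Sample size. Eight CPHSSs per arm in two strata comes from Allocation. Assumptions of this check: a two-sided test (not stated, but 186 matches only two-sided), equal cluster sizes, and a between-cluster t reference.

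**1. Individually randomized size.** With pooled rate 0.60,

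n per arm = [1.960 × √(2 × 0.6 × 0.4) + 0.842 × √(0.25 + 0.21)]² / 0.20² = 93.0, so 186 in total. This matches exactly. With a continuity correction the total would be 206, which does not match.

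**2. Clustered size.** Design effect = 1 + (m − 1) × ICC. With m = 30, 1 + 29 × 0.05 = 2.45, and 186 × 2.45 = 455.7, so 456. The article does not state m = 30; it is inferred because it reproduces the figure. Solving for exactly 16 clusters, N = 186 × 0.95 / (1 − 186 × 0.05/16) = 422, so 456 is 34 above the normal-theory minimum.

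**3. Normal-theory power at 456.** m = 456/16 = 28.5 and the design effect is 1 + 27.5 × 0.05 = 2.375.

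- Unpooled: SE = √(0.46 × 2.375/228) = 0.0692; 0.20/SE = 2.889; power 82.4%.
- Pooled: SE = √(0.48 × 2.375/228) = 0.0707; 0.20/SE = 2.828; power 80.7%.

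The stated 80% is therefore met under normal theory.

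**4. Power with a t reference.** The same ratios are used as noncentrality parameters of a t distribution, at ICC 0.05:

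| Clients analysed | Variance | Normal | t, 14 df | t, 13 df |
|---|---|---|---|---|
| 456 | unpooled | 82.4% | 76.6% | 76.2% |
| 456 | pooled | 80.7% | 74.9% | 74.4% |
| 512 (no loss) | unpooled | 84.0% | 78.5% | 78.0% |
| 512 (no loss) | pooled | 82.4% | 76.7% | 76.2% |

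A beta-binomial simulation with a cluster-level t-test on 14 df, at 28, 29 and 30 clients per CPHSS, gave 75.3%, 76.5% and 76.3%.

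**5. Dependence on the ICC** (456 clients):

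| ICC | t, 14 df, unpooled | t, 13 df, pooled |
|---|---|---|
| 0.02 | 91.3% | 89.9% |
| 0.03 | 86.5% | 84.6% |
| 0.04 | 81.5% | 79.4% |
| 0.05 | 76.6% | 74.4% |

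Power reaches 80% at ICC 0.043 in the first column and 0.039 in the second. At ICC 0.05, the difference from 50% detectable with 80% power is 20.8 to 21.4 points across the four combinations of variance and df.

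**6. Loss and recruitment.** 456 × 1.10 = 501.6, which truncates to 501. The size that leaves 456 after 10% loss is 456/0.90 = 506.7, so 507. The target per CPHSS gives 32 × 16 = 512. After 10% loss, 501 leaves 450.9 and 512 leaves 460.8. On t with 14 df (unpooled), power is 76.5% at 451, 76.6% at 456 and 76.8% at 461.

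**The case against.** The strongest reply is that the calculation is not wrong on its own terms. The figure of 186 is exact, 456 exceeds the normal-theory minimum, and the article calls ICC 0.05 a cautious upper limit. Over most of the range considered, the design keeps 80% power or more even with the t reference. This stands, and it limits the point to ICCs above about 0.04. It does not remove it, because the article attaches its 80% to ICC 0.05 and not to a lower value.

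Stronger readings that a reader might infer are not supported:

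- *That 75 to 77% is simply the trial's true power.* It is conditional on ICC 0.05 and on a between-cluster t reference, and the article names no degrees-of-freedom method. The 13-df figures are also somewhat severe: they charge a degree of freedom for the stratum without crediting any variance that it explains.
- *That the analysis will run at about 7% type I error.* This would follow from comparing the statistic with 1.96, but nothing in the article says that will be done. The degrees-of-freedom method is commonly left to an analysis plan, which is not shown.
- *That unequal cluster sizes lower power further.* They would, but the article sets a common target of 32 per CPHSS and gives no basis for any coefficient of variation.
- *That the trial will fall short of 456.* It would only if 501 governs. The target per CPHSS in the same sentence leaves 461.

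**Conclusion.** The point holds in a limited form. At the article's own inputs (50% versus 70%, ICC 0.05, 456 clients, 8 CPHSSs per arm), power is about 74 to 77% rather than 80%, a shortfall of roughly 3 to 6 points. This assumes a two-sided 5% test, equal cluster sizes and a t reference on 13 to 14 df. The plan's own margin does not absorb it: with all 512 recruits analysed and no loss, power is still about 76 to 78%. The shortfall disappears at an ICC of about 0.043 or lower (about 0.039 on the least favourable convention), or for a difference of about 21 points at ICC 0.05.

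The recruitment sentence contradicts itself (501 against 512) and uses the wrong form of inflation. The consequence for power is about 0.2 points at most between 451 and 456, so this is a correction of the text and not a threat to the trial.

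**What to change.** Restate the power along these lines: 456 analysable clients in 16 CPHSSs give about 75 to 77% power for 50% versus 70% at ICC 0.05, two-sided 5%, t on about 14 df, equal cluster sizes. Add that power is about 81% at ICC 0.04 (79.9% with pooled variance, 81.5% unpooled), and that at ICC 0.05 the design has 80% power for a difference of about 21 points.

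Replace 501 with 512 (32 per CPHSS × 16), which also covers the correctly inflated 507.

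The cost is wording and a slightly less favourable stated power. No CPHSSs are added, and no clients beyond the 32 each already planned. Holding 80% at ICC 0.05 by size alone would take about 572 to 649 analysed clients on 14 df, or 592 to 674 on 13 df. Since 0.05 is the top of the range considered, restating the power is the proportionate change.

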#### Analysis plan

We will perform a descriptive statistical analysis of organizational (CPHSS/health professionals) and socio-demographic (clients/health professionals) characteristics in order to assure the comparability of the intervention and control groups. Potentially confounding variables, if any, will be introduced as covariates in mathematical modeling analysis. Multilevel modeling will be used to take the hierarchical structure of the data into account by specifying random effects at each of the 2 levels: 1) CPHSS and 2) client. For each outcome analyzed, according to the type of variable (continuous or categorical), the goodness of fit and the assumptions of each model will be assessed. Statistical analysis will be performed using the SAS statistical package [46]. The primary outcome, i.e. the proportion of clients reporting an active role in the decision-making process, will be analyzed through multilevel logistic regression using the GLIMMIX procedure of the SAS program. The least squared mean proportions will be estimated and compared to assess the effect of the intervention on the primary outcome. Secondary outcomes will be comparisons between the 2 groups (intervention, control) using multilevel modeling. The *P* value will be adjusted for any multiple comparison tests. Adjustment for multiple comparisons will only be made for secondary outcomes, using the Bonferroni method. This will avoid significant results being due to chance alone. Analysis will be performed after the pre-intervention data collection (for providing performance feedback during the workshop) and at the end of the trial. We will explore the impact of differences between male and female clients on the primary outcome.

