### Losses to follow-up

We expect few losses to follow-up in this trial due to the stability of the population studied, only one data collection point for clients and caregivers, and additional measures to minimize loss. All study participants will be included in the analysis as part of the group to which they were randomized, regardless of whether they completed the study or not (‘Intention-to-treat’ analysis). ‘Worst-case scenario’ sensitivity analysis will be performed for missing data on clients.

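### The primary model does not name the urban/rural randomisation stratum, and its covariate rule would not normally pick it up; the client random effect needs one clarifying phrase

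*Protocol article*

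**What the plan says.** In the Protocol article, Allocation of participants to trial groups: "The unit of randomization will be the CPHSS with stratification by urban or rural setting". The same section fixes the allocation at 2 urban and 6 rural centers in each arm.

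The Analysis plan section says that the primary outcome "will be analyzed through multilevel logistic regression using the GLIMMIX procedure of the SAS program" and that least-squares mean proportions will be compared. It describes the multilevel structure, for outcomes in general, as "specifying random effects at each of the 2 levels: 1) CPHSS and 2) client". Its only statement on covariates follows a descriptive comparison of the two arms: variables that may confound, should there be any, are added to the model. Urban/rural setting is neither named as a model term nor ruled out.

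Under Outcome measures, the primary outcome is a single five-option question, dichotomised into active or passive role. Under Losses to follow-up there is "only one data collection point for clients and caregivers". Under Trial design and setting, different clients are recruited before and after the intervention. Each client therefore gives one binary answer.

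**The concern.** A variable used to restrict the randomisation normally belongs in the primary model. Stratification removes the urban-rural difference from the true variability of the arm comparison. If the model has no stratum term, that difference stays in the estimated between-center variance, so the standard error is too large. With only 16 centers, between-center variance largely decides the power.

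The covariate rule does not repair this. It looks for differences between arms, and the numbers of urban and rural centers are equal in both arms by construction.

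The wording on random effects raises a smaller point. Read literally, it asks for a client random effect as well as a center one. For a binary outcome measured once per client, the data cannot separate a client variance from ordinary Bernoulli variation, and the least-squares mean proportions would depend on whatever value the software settled on.

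**Working it through.** **Inputs from the Protocol article (Sample size; Allocation).** 50% versus 70% active role; "with 80% power, and a 5% significance level"; ICC 0.05; 16 CPHSSs; 456 clients before allowance for loss; 2 urban and 6 rural centers per arm.

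**The plan's own figures.** Two-sided test, pooled variance, mean proportion 0.6:

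n per arm = [1.96 × √(2 × 0.6 × 0.4) + 0.8416 × √(0.25 + 0.21)]² / 0.2² = (1.3579 + 0.5708)² / 0.04 = 93, so 186 in total, as stated.

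The design effect with 30 clients per center (my assumption; the article gives no cluster size at this step) is 1 + 29 × 0.05 = 2.45, and 186 × 2.45 = 455.7, so 456. Neither figure depends on the stratum or on the client random effect. Per center, 456 / 16 = 28.5.

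**Stratum: size of the variance at issue.** The urban-rural gap g is an assumption. Hold the total between-center variance at 0.05 × 0.25 = 0.0125. With a quarter of centers urban, the stratum contributes g² × 0.25 × 0.75:

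- g = 0.10: 0.001875, which is 15% of 0.0125
- g = 0.15: 0.00421875, which is 34% of 0.0125

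The variance of a center mean is 0.0125 + 0.25 × 0.95 / 28.5 = 0.02083. Balanced strata remove the stratum part from the true variance of the arm difference. An unadjusted model puts it back into the residual as 16 × 0.1875 g² / 14 = 0.2143 g².

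| Gap | True variance per center mean | Expected residual, stratum omitted | SE ratio |
|---|---|---|---|
| 10 points | 0.02083 − 0.00188 = 0.01896 | 0.01896 + 0.00214 = 0.02110 | √(0.02110 / 0.01896) = 1.05 |
| 15 points | 0.02083 − 0.00422 = 0.01661 | 0.01661 + 0.00482 = 0.02144 | √(0.02144 / 0.01661) = 1.14 |

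So the reported standard error is about 5% or 14% too large.

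**Stratum: effect on the test.** Simulated trials with 16 centers and 28 to 29 clients each; center proportions regressed on arm (14 df) or on arm plus stratum (13 df). This is a proxy for the GLIMMIX model.

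| Assumed gap (total ICC fixed at 0.05) | Type I error, omitted vs included | Power, omitted vs included |
|---|---|---|
| 10 points | 4.0% vs 5.0% | 76% vs 79% |
| 15 points | 2.7% vs 4.7% | 76% vs 83% |

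Repeat runs moved these levels by a point or two. The gain stayed at about 3 points of power at a 10-point gap and 7 to 8 at a 15-point gap.

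If the gap adds to the ICC of 0.05 instead of forming part of it, power is 73% vs 76% at 10 points, 67% vs 74% at 15 and 62% vs 76% at 20.

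With no gap, including the stratum costs 0.3 to 0.6 point. The non-central t calculation at 456 clients agrees: 76.6% on 14 df, 76.1% on 13 df.

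**Client random effect.** Suppose a client intercept with variance s² is added on the logit scale. The observed proportion in an arm is then the average of expit(b + s × z) over standard normal z. For each s² a value of b can be found that gives exactly 50% in one arm and 70% in the other, so the fit is the same. At 50%, b = 0, so the back-transformed mean in the intervention arm is OR / (1 + OR).

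| Client variance | Conditional OR | Back-transformed mean, intervention arm |
|---|---|---|
| 0 | 2.33 | 70% |
| 1 | 2.77 | 73.5% |
| 4 | 3.99 | 80% |
| 9 | 6.19 | 86% |

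The same data support every row. One binary answer per client cannot choose between them.

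**The case against.** The strongest reply is that this is silence in a condensed article. The Analysis plan names a model class and an estimand; it lists no fixed effects and does not say that confounders are the only covariates allowed. A full protocol or SAP may already include the stratum. That stands against one tempting inference, that the plan has decided to leave the stratum out or departs from its own design. The text does not show that. What remains is that the one covariate rule it states works through observed differences between arms and so would not normally select this factor. The route is not wholly closed: allocation balances numbers of centers, not of clients, and uneven recruitment could leave some client-level imbalance.

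The gaps of 10 and 15 points are assumed, and the test is a proxy. Both are true, so the sizes are indicative. The direction does not depend on them.

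A reader might also infer that the primary test is invalid. It is not: omission makes it conservative, with no bias and no excess of false positives.

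On the client term, a reader might call the wording an outright error. It may be no more than ordinary two-level language, in which the client is level 1 and the random term is the residual. The sentence covers all outcomes, and on that reading it is correct for the continuous scales. Only a literal client intercept on the binary outcome would be wrong, and the article does not clearly ask for one.

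Finally, one might extend the point to the providers' intention measure, taken at study entry and exit. How that is modelled is a detail for the SAP and is not a finding here.

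**Conclusion.** The point holds as a recommendation to state the model explicitly. The stratum is fixed by the design, is not named in the primary analysis, and would not normally enter through the covariate rule shown. If it is left out and urban and rural centers differ, the trial loses about 3 points of power at a 10-point gap and 7 to 8 at a 15-point gap, and the actual type I error falls to about 4% and 3%. These figures assume a total ICC of 0.05, 28 to 29 clients per center and a cluster-level test in place of GLIMMIX. If the two settings have the same rate, nothing is gained and about half a point of power is spent. The client random effect is a matter of clarification: harmless if it means the level-1 unit, not estimable if it means an added intercept for the primary outcome.

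**What to change.** In the Analysis plan, state the primary model as a logistic model for active role with fixed effects for arm and urban/rural setting and a random intercept for CPHSS. In the same sentence, say that the client is the level-1 unit and that no separate client random intercept is fitted to the binary primary outcome.

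The cost is wording, plus one between-cluster degree of freedom for the stratum. The sample size, the recruitment target and data collection are unchanged, since setting is already known for every center at randomisation.

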### Outcome measures

The primary outcome of interest is the assumed role in the decision making. We will use the modified version of the Control Preferences Scale [28] designed to assess the assumed role in the decision-making process reported by the client or the caregiver [29]. The scale consists of a single question to assess the client’s perception of locus of control over the decision-making process. This is the scale used most in studies assessing the implementation of SDM in clinical practices [18,30]. It is responsive to change and correlates with patients’ as well as with clinicians’ reported levels of patient involvement [31]. Response options (n = 5) are as follows: A) I made the decision; B) I made the decision after seriously considering my providers’ opinions; C) My providers and I shared the responsibility for the decision making; D) My providers made the decision after seriously considering my opinion; E) My providers made the decision. A and B represent a client-controlled decision-making process, C represents a shared decision-making process, and D and E represent a practitioner-controlled decision-making process [29]. We will combine A, B and C to identify the proportion of clients reporting an active role in the decision-making process, and we will combine D and E to identify a passive role. We will perform our analysis by assessing the increase in the percentage of clients reporting an active role.

Measures of secondary outcomes will be collected. More specifically, in clients and caregivers, we will assess their preferred and chosen option (remain at home or move to care facility); decisional conflict using the Decisional Conflict Scale [32,33]; decisional regret using the Decisional Regret Scale [34]; HR-QoL (only in client) using 2 subscales from the Nottingham Health Profile: Social Isolation and Emotional Reactions [35-38]; and burden of care (only in caregivers) using a validated scale [39-42].

In providers, at study entry and exit, we will assess their intention to engage in SDM behaviors in the context of an IP home-care team sharing the decision with elderly people about whether to stay at home or move to another location.

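### The least-squares mean proportions chosen to summarise the primary effect are cluster-specific values, not the percentage of clients that the trial defines and was sized on; the gap is small and cheap to close

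*Protocol article*

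**What the plan says.** Three parts of the protocol article bear on the size of the primary effect.

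- **Outcome measures** dichotomises the modified Control Preferences Scale into active (A, B, C) and passive (D, E) and then says: "We will perform our analysis by assessing the increase in the percentage of clients reporting an active role". The quantity is a percentage of clients.
- **Sample size** uses the same scale, an absolute difference in percentages: "In order to detect a difference of 20% (50% to 70%) between the intervention group and the control group after the intervention with 80% power".
- **Analysis plan** specifies multilevel logistic regression in SAS GLIMMIX with a random effect for CPHSS. Potential confounders, if any are found, enter as covariates. The effect summary is then fixed: "The least squared mean proportions will be estimated and compared to assess the effect of the intervention on the primary outcome".

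The Analysis plan does not say whether these proportions are averaged over the CPHSSs and the clients.

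**The concern.** In a random-intercept logistic model, a least-squares mean is a linear predictor on the logit scale. The CPHSS effect is set to zero and covariates are held at average values. Its inverse logit is the probability of an active role for a notional average client in a median CPHSS. The percentage of clients reporting an active role is instead an average of probabilities over clients and over CPHSSs. The inverse logit is nonlinear, so the two agree only at 50% or when there is no heterogeneity.

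The headline proportions and their difference would therefore answer a slightly different question from the one in Outcome measures and Sample size. The mismatch is systematic, and recruiting more clients would not remove it. What is at stake is how the size of the effect is reported, not whether an effect is detected.

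**Working it through.** **Inputs from the protocol article, Sample size:** 50% and 70%; 80% power; 5% significance level; ICC scenarios from 0.02 to 0.05, with 0.05 used; 16 CPHSSs; 456 clients, or 456/16 = 28.5 per CPHSS. **Assumptions made here:** a normally distributed CPHSS effect on the logit scale; ICC read on the proportion scale at p = 0.6 unless noted; a two-sided test, since sidedness is not stated.

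**1. The plan's own figure.** The article says "we would require a total of 186 clients for an individually randomized trial". With a pooled variance and no continuity correction:

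n per arm = [1.960·√(2·0.6·0.4) + 0.842·√(0.5·0.5 + 0.7·0.3)]² / 0.20² = 93, so 186 in total. This reproduces exactly.

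At 456 clients the design effect is 1 + (28.5 − 1)·0.05 = 2.375. The effective size is 456/2.375 = 192, and power is 81.2%. The sizing is on the percentage scale, and nothing below changes it.

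**2. From ICC to random-intercept variance.** Solving numerically for the logit-scale variance σ² that gives the stated ICC: ICC 0.02 gives σ² = 0.087; ICC 0.05 gives σ² = 0.230.

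**3. From client percentage to least-squares mean.** For a true percentage p, find η such that E[expit(η + σZ)] = p, with Z standard normal, by Gauss-Hermite integration. The least-squares mean proportion is expit(η). At p = 0.50 it is 0.500 by symmetry.

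At p = 0.70 with σ² = 0.230, η = 0.891 and expit(0.891) = 0.709. The difference is 0.709 − 0.500 = 20.9 points against a true 20.0.

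| True percentages | ICC | Least-squares mean difference | True difference |
|---|---|---|---|
| 50 vs 70 | 0.02 | 20.4 | 20.0 |
| 50 vs 70 | 0.05 | 20.9 | 20.0 |
| 50 vs 70 | 0.05 (latent scale, σ² = 0.173) | 20.7 | 20.0 |
| 60 vs 80 | 0.05 | 20.5 | 20.0 |
| 70 vs 90 | 0.05 | 19.9 | 20.0 |
| 80 vs 90 | 0.05 | 9.7 | 10.0 |
| 50 vs 50 | 0.05 | 0.0 | 0.0 |

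**4. Client covariates.** If prognostic covariates enter the model, their logit-scale variance adds to σ² in step 3. The article gives no value, so the following are assumptions, all at ICC 0.05 and 50% versus 70%:

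- added variance 0.25: 71.8% versus 50.0%, a difference of 21.8 points;
- added variance 0.5: 22.6 points;
- added variance 1.0: 24.1 points.

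**5. Against sampling error.** SE of the difference at 456 clients = √[2.375·(0.25 + 0.21)/228] = 6.9 points. The largest gap without covariates, 0.9 point, is 0.9/6.9 ≈ 0.13 SE.

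**6. Simulation.** In 1,500 simulated trials of 16 clusters of 28 clients, fitted by restricted pseudo-likelihood (assumed to be the GLIMMIX default), the mean least-squares mean difference was 20.3 points and the mean raw difference 19.8. The gap was about 0.5 point.

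**The case against.** The strongest reply is that the article is condensed. It names the model, the software and the summary, and leaves inverse linking, weights and averaging to a fuller plan. Least-squares mean proportions are also a recognised GLIMMIX output, so preferring another summary might be taste. This stands in part: the text does not exclude averaging over CPHSSs. But the summary itself is stated, not omitted, and in ordinary use least-squares means do not average over the random effect.

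The objections to size and direction stand. Four stronger readings are tempting, and the document does not support them:

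- *Least-squares means overstate the difference in general.* They do at the planned 50% versus 70%, but slightly understate it when both rates are high. The 50% baseline is only an expected value.
- *The overstatement reaches 4 points.* That needs an assumed covariate variance of 1.0. Covariates enter only if confounders are found, and no variance is given.
- *An effect short of 20 points could be reported as reaching the target.* Twenty points is a sizing assumption; the article nowhere makes it a criterion of success. At ICC 0.05 without covariates, a true 19-point effect (50% versus 69%) gives 19.9.
- *Urban CPHSSs would count as half instead of 4 of 16.* Setting stratifies the randomisation, but the Analysis plan does not name it as a covariate. Under assumed urban-rural gaps of 10 to 30 points, equal weighting moves the difference by about −0.7 to +2.1 points, so even the direction is open.

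**Conclusion.** The point holds as a mismatch between the stated effect summary and the trial's own question. At the planned rates and the article's ICC range, without covariates, the difference is overstated by about 0.4 to 0.9 point on 20. It would be more with prognostic client covariates, about 1.8 points at an assumed added logit variance of 0.25 with ICC 0.05. With both rates high it is slightly understated. The test of no effect, the power and the sample size are unaffected.

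This rests on a normal CPHSS effect, the ICC read as in the working, and the standard meaning of least-squares means. It is a worthwhile improvement, not a material flaw.

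**What to change.** In the Analysis plan, name the primary effect as the difference in marginally standardised proportions. From the fitted model, predict each client's probability under both arms, average over clients and over the CPHSS random-effect distribution, and report the two percentages and their difference.

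Give a 95% confidence interval with a small-sample correction: t-based, with cluster-level degrees of freedom (16 − 2 = 14 before any cluster-level covariate). An uncorrected bootstrap of 16 clusters should not be used. Report the odds ratio as a supporting figure.

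The cost is a sentence of wording and slightly more programming than a least-squares means statement. The point estimate may move by about a point in either direction.
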